#### Economic outcomes

The CHU9D will also be used to derive health state utility values by using the previously published value set, reflecting Australian adolescents’ preferences, to derive quality-adjusted life years (QALYs) [40].

Health service use will be assessed using a modified Resource Utilization Questionnaire (RUQ) [29]. This 21-item questionnaire was developed to measure the health services and costs of health care. This questionnaire has been modified from the version used in the Young Minds Matter Survey to enable self-report by adolescents and will ask which health professionals participants have seen in the past 4 weeks for their mental health (number of the visits, location, and costs of visits), and medications taken for emotional or behavioral concerns in the past 4 weeks (type, dosage), and days of missed school [28]. Resource use and unit costs will be combined to derive a total cost for each participant.

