### Eligibility criteria {10}

Eligible participants will be male senior secondary school students in year 10, 11, or 12 who are enrolled to take part in a *Breaking the Man Code* workshop in 2021 or 2022 within their school and have parental/guardian informed consent.

School inclusion:
Request a *Breaking the Man Code* workshop for their year 10, 11, or 12 males in 2021 or 2022.Agree to schedule the workshop within either the intervention period or the waitlist period (after the trial is complete) as instructed by the researchers.Agree to distribute study information to parents of boys enrolled in the workshop and to allocate two class times, 6–8 weeks apart, for students to complete the baseline and follow-up questionnaire.

Student inclusion:
Student within a participating school in years 10, 11, or 12Self-identified maleEnrolled to take part in a *Breaking the Man Code* workshopParent has provided consent for them to take part in the trial

There are no exclusion criteria.

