#### Economic outcomes

The economic outcome of the intervention will be determined in comparison to the waitlist control group from a health care perspective and a partial societal perspective. The CHU-9D data will also enable the calculation of quality-adjusted life years (QALYs) that will be used in a cost-utility analysis. Key costs and their measure(s) include (i) intervention costs, (ii) parents’ productivity losses (based on the number of days their son is absent from school), and (iii) health care service costs during the trial follow-up period (collected using a modified Resource Utilization Questionnaire (RUQ) [29]).

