For schools in the waitlist group, soon after randomization, the schools will schedule a class time for all the male students who are enrolled to take part in the workshop. The school will advise the researchers of this class time and the researchers will direct Logicly to send an email to students with parental consent containing a link to the Plain Language Statement, assent form, and baseline questionnaire. The school staff member will activate the baseline questionnaire within the class time using a link provided to them by Logicly. After reading the Plain Language Statement and providing their assent, the students will have access to complete the online survey which will take about 20 min. The schools will then provide school as usual for the students over the following weeks. Schools will be asked to schedule a second class time for students to complete the follow-up questionnaire 6 to 8 weeks after the baseline questionnaire. The staff member will activate the questionnaire and the students will complete it. They will receive the workshop after the second survey has been completed by the students.

In either group, if a student has completed the baseline questionnaire, but cannot locate the email for the follow-up questionnaire, then an automated process will enable the teacher to provide the student email to Logicly who will resend the email.

If schools or individual participants withdraw from the trial at any time (prior to baseline or follow-up questionnaire assessment), the data provided by participants up to that point will be included in the trial.

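### Visits and medications are recalled over 4 weeks but costed as use over a 6–8 week follow-up, so 2–4 weeks of use are never recorded

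*Protocol article*

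**What the plan says.** Under Outcomes {12}, Economic outcomes, the protocol lists three cost components: the intervention itself, parents' lost productivity derived from school absence, and "health care service costs during the trial follow-up period". The last is collected with the modified RUQ.

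Under Plans for assessment and collection of outcomes {18a}, Economic outcomes, the RUQ "will ask which health professionals participants have seen in the past 4 weeks for their mental health". It also covers "medications taken for emotional or behavioral concerns in the past 4 weeks (type, dosage), and days of missed school". The 4-week window is attached to professionals seen and to medications; missed school comes last in the list with no window of its own. The section then says: "Resource use and unit costs will be combined to derive a total cost for each participant".

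On timing, participating schools must "allocate two class times, 6–8 weeks apart, for students to complete the baseline and follow-up questionnaire" (Eligibility criteria {10}). Waitlist students "complete the follow-up questionnaire 6 to 8 weeks after the baseline questionnaire" (Participant timeline {13}). In the intervention arm, baseline falls in the 2 weeks before the workshop and follow-up 4–6 weeks after it. The outcome sections name 8 weeks post-baseline as the time point. Section {18a} describes the follow-up questionnaire as the baseline one repeated without demographics and with some added open-ended questions for the intervention group.

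**The concern.** The period to be costed and the period asked about differ. The costed period is the follow-up, 6–8 weeks. The question reaches back 4 weeks from the day of the follow-up questionnaire. The baseline RUQ cannot fill the gap, because its 4 weeks lie before baseline.

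At stake is the cost side of the cost-utility analysis. If the follow-up answers are multiplied by unit costs and called the participant's total, visit and medication costs are incomplete. If QALYs are calculated from baseline to follow-up, these costs and the QALYs in the same ICER cover different lengths of time. The sensitivity analyses listed under Methods for additional analyses {20b} vary intervention costs, the intervention pathway and the proportion receiving it; the recall gap is not among them.

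**Working it through.** The protocol gives no figure for the share of follow-up that the recall covers, so there is none to reproduce. The check uses only its stated windows.

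**Inputs**
- Recall for visits and medications: 4 weeks ({18a}, Economic outcomes).
- Baseline to follow-up, L: 6–8 weeks (Eligibility criteria {10}, both arms; {13} and {18a}, waitlist arm).
- Intervention arm, baseline to workshop, a: 0–2 weeks ({13}, {18a}).
- Intervention arm, workshop to follow-up, b: 4–6 weeks ({13}, {18a}).

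**1. Share of follow-up not recorded** = (L − 4)/L
- L = 6: 2/6 = 33%
- L = 7: 3/7 = 43%
- L = 8: 4/8 = 50%

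At a constant weekly rate of use (assumption), unscaled visit and medication costs are understated by these same percentages.

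**2. Intervention arm from its component windows**, L = a + b
- Shortest: 0 + 4 = 4 weeks, gap 0/4 = 0%.
- Longest: 2 + 6 = 8 weeks, gap 4/8 = 50%.

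The 6–8 week school criterion would narrow this to 33–50%, but the component windows alone do not enforce it.

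**3. Post-workshop time missed** = (b − 4)/b
- b = 4: 0/4 = 0%
- b = 5: 1/5 = 20%
- b = 6: 2/6 = 33%

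Because b is at least 4, the recall window always lies after the workshop. Any time between baseline and workshop is always in the unrecorded part.

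**4. Between-arm difference, illustration.** Assume equal L in both arms, a common weekly cost c in the waitlist arm and before the workshop, and a constant weekly cost d after it.
- True difference: b(d − c). Recorded difference: 4(d − c). Share lost: (b − 4)/b = 0–33%, smaller than the 33–50% in step 1.
- Scaling both arms by L/4 (6/4 = 1.5 to 8/4 = 2.0) gives L(d − c). That exceeds the true difference by a factor L/b, for example 6/4 = 1.5 when a = 2 and b = 4. Simple scaling applies a post-workshop rate to pre-workshop weeks.
- The sign depends on whether d is above or below c, which the protocol cannot tell us.

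**5. Cost and QALY periods.** If QALYs run from baseline to follow-up (assumption), they span 6/52 = 0.115 to 8/52 = 0.154 years, against 4/52 = 0.077 years of recorded visits and medications.

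**The case against.** The strongest reply is that this is a condensed article. The sentence on combining resource use with unit costs does not rule out scaling to the interval, and an analysis plan that is not shown may specify it. At a constant rate, scaling removes the understatement in each arm's total. This stands in part: the understatement is conditional on no scaling. But the recall window is a data-collection choice fixed here, and scaling extrapolates weeks that nobody measured. Step 4 shows that it can also distort the contrast.

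A fixed 4-week window has merits too. It is the same length in both arms, matches the baseline RUQ, and is easier to recall. That stands as a cost of changing it.

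A reader might also infer more than the documents support:
- *School absence is recalled for 4 weeks only.* No window is stated for missed school, so no shortfall can be calculated for productivity losses.
- *The whole ICER numerator covers 4 weeks.* Intervention costs are a separate component and do not depend on recall.
- *Up to half of the incremental cost is lost.* The half is a share of follow-up time at 8 weeks. Workshop effects can arise only after the workshop, where 0–33% of the time is missed.
- *The gap favours the workshop.* That needs extra service use concentrated in the missed weeks. The handover described under Adverse event reporting {22} is to school staff, whereas the RUQ items concern health professionals. If the workshop reduced early use, the bias would run the other way.

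**Conclusion.** The concern holds for health professional visits and medications. As written, the RUQ cannot supply costs for the stated period: 33–50% of a 6–8 week follow-up is unrecorded, with 0–50% possible in the intervention arm by its component windows. The understatement of these two components by 33–50% assumes a constant rate of use and no scaling. The mismatch with QALYs assumes that these run from baseline to follow-up, which is the natural reading of a utility measure asked at those two points but is not stated. The size of the effect on the between-arm cost difference is uncertain and may be smaller; its direction is unknown. The issue is confined to the economic evaluation. It is worth correcting, but it does not bear on the primary outcome or its analysis.

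**What to change.** - **Preferred:** in both arms, word the follow-up RUQ items on visits, medications and missed school days to cover the time since the student completed the first questionnaire. This means rewording items in an online form and notifying the ethics committee. The downsides are slightly longer recall that varies by student, and a window that differs from the baseline RUQ.
- **For students already surveyed, or if the 4-week wording is kept:** scale 4-week visit and medication costs to each student's actual baseline-to-follow-up interval and state the constant-rate assumption. Vary it in the sensitivity analyses under {20b}, including a version that does not apply the post-workshop rate to pre-workshop weeks in the intervention arm. This needs no change to the instrument, but the missing weeks remain extrapolated.
- **In either case:** state one common horizon for costs and QALYs, give the recall window for missed school days, and reconcile the economic text under {12} with the questionnaire description and timing under {18a}.

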#### Participant’s perception and impact of the intervention

In addition to these standardized measures, in the follow-up questionnaire, the intervention group will be asked a set of closed and open-ended questions regarding their perceptions of the workshop (What parts did you like the most/least? Did you change your attitudes or behaviors in any of the following ways?) and the impact of the workshop on their lives (Did the workshop change your ideas about what sort of man you’d like to be? Did the workshop change the way you talk with your mates/family about personal stuff?).

The questionnaires are available from the principal investigator.

### Plans to promote participant retention and complete follow-up {18b}

The study Advisory Group, Consumer Reference Panel, and other researchers who are working in school-based research will be consulted with regarding strategies to enhance retention of schools and students in the trial. Research that ensures the quality and impact of the *Breaking the Man Code* workshops will likely be appealing to schools who receive the workshops. Schools will also be provided with a one-off payment of A$800 after their involvement in the trial to compensate for the administrative burden. This payment will act to reduce any barriers to school participation. Students will not be incentivized or coerced to take part as it is the requirement of the ethics approvals. The Plain Language Statement will provide information to students about the benefits of participation.

### Data management {19}

All data will be self-report and entered by students into a secure online questionnaire that will be managed by Logicly. The questionnaires will be online and programmed with a logic that minimizes missing data by alerting participants to unanswered questions and maximizes data quality (e.g., range checks for data values). At the end of the data collection period, all data will be provided in the deidentified form to the researchers. Data will be stored in accordance with Monash University data storage policies [41].

### Confidentiality {27}

During the trial, the data will be stored by Logicly. Data will only be stored in electronic form and will be held securely on password-protected computers. Once data collection is finished, deidentified data will be provided to the researchers named on this protocol. Any hard copy printouts of data will be held in locked filing cabinets in locked offices. At the end of the project, deidentified coded quantitative data collected in the questionnaires will be uploaded to the Monash University Research Repository to be held for a maximum of 5 years after the last publication from the trial researchers. Individual questionnaire responses will be aggregated for analysis and reporting. No identifying information about schools or participants will be included when reporting findings from the trial.

### Plans for collection, laboratory evaluation, and storage of biological specimens for genetic or molecular analysis in this trial/future use {33}

Not applicable, no biological samples were collected.

## Statistical methods

### Statistical methods for primary and secondary outcomes {20a}

Descriptive statistics will be used to summarize school and participant characteristics between study groups. Analysis will use an intention to treat (ITT) approach, where participants will be analyzed in the study group to which they were randomized. Statistical analysis will be conducted using Stata Software 15 [42].

For the primary analysis, linear mixed effect models will be used to estimate the difference in mean change in GHSQ scores at follow-up between the study groups, with random effects for school and fixed effects for study group, baseline GHSQ scores, and stratification factors (location of the schools, state, and mode of workshop delivery). The estimated intervention effect will be reported as the difference in mean GHSQ scores between intervention and control groups, with 95% confidence interval and *p*-value. Similar analysis will be undertaken for secondary outcomes (conformity to masculine norms, depression risk, perceived social support, and quality of life).

#### Economic evaluation

Generalized linear models will be used to assess mean difference in costs and QALYs in the two study groups. For both groups, mean values of costs and QALYs will be reported, as well as mean differences between the groups. An incremental cost-effectiveness ratio (ICER) will be calculated as the difference in average cost between the groups, divided by the difference in average QALYs. Uncertainty in the data will be handled by using nonparametric bootstrapping from the distribution of the observed cost/QALY pairs (e.g., 1000 simulated replications) to determine confidence intervals (CIs) and presented in a cost-effectiveness plane along with a cost-effectiveness acceptability curve.

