## Data collection and management

### Plans for assessment and collection of outcomes {18a}

Outcome measures will be collected from students at baseline after randomization of schools. For the intervention group, data will be collected at baseline within 2 weeks of the intervention being delivered. The follow-up questionnaire will be administered 4–6 weeks after the workshop. For the waitlist control group, baseline and follow-up data collection will occur 6–8 weeks apart before the workshop is delivered.

For both groups, the baseline and follow-up questionnaires will be administered online within an allocated class time. The baseline questionnaire will include demographic questions and the measures related to the primary, secondary, and economic outcomes that are described below. The follow-up questionnaire will be a repeat of the baseline questionnaire, minus the demographic questions, with the addition of some open-ended questions for the intervention group.

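### As written, the ICER and its bootstrap name no baseline adjustment, although CHU-9D utility and resource use are measured at baseline; adjusting costs no new data and would make the QALY difference more precise

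*Protocol article*

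**What the plan says.** The Economic evaluation section of the protocol article has three relevant statements.

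- Model: "Generalized linear models will be used to assess mean difference in costs and QALYs in the two study groups". No covariates are listed.
- Estimator: "An incremental cost-effectiveness ratio (ICER) will be calculated as the difference in average cost between the groups, divided by the difference in average QALYs".
- Uncertainty: "nonparametric bootstrapping from the distribution of the observed cost/QALY pairs", with about 1000 replications, leading to a cost-effectiveness plane and an acceptability curve.

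The baseline data exist. Section {18a} states: "The baseline questionnaire will include demographic questions and the measures related to the primary, secondary, and economic outcomes that are described below". It adds: "The follow-up questionnaire will be a repeat of the baseline questionnaire, minus the demographic questions". The Economic outcomes text under data collection says that the CHU-9D will be used "to derive health state utility values by using the previously published value set, reflecting Australian adolescents’ preferences, to derive quality-adjusted life years (QALYs"). It does not say how the two utilities are combined into a QALY.

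The clinical analysis is set up differently. Section {20a} gives the primary model a random school effect and "fixed effects for study group, baseline GHSQ scores, and stratification factors". It plans similar models for the secondary outcomes, one of which is quality of life on the CHU-9D. Section {20b} adds further covariate adjustment for the primary and secondary outcomes only. Its economic sensitivity analyses do not mention baseline values.

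**The concern.** The same questionnaire is handled in two ways. As a secondary outcome, the CHU-9D is compared after adjustment for its baseline value and the strata. As the source of the ICER denominator, it enters, on a plain reading, as a difference between group averages with observed pairs resampled.

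This matters more for QALYs than for an ordinary follow-up score. In a two-point area under the curve, half the weight falls on the baseline utility, which the workshop cannot have changed. A baseline difference between arms then counts as part of the QALY difference, and the variation in baseline utility adds noise.

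Some imbalance should be expected. Only about 40 schools are randomised, and parental consent and the baseline survey follow randomisation at schools that know their allocation. Over 6 to 8 weeks any true QALY difference will be very small, so modest noise in the denominator can dominate the ratio.

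**Working it through.** **The plan's own figure.** The article gives no precision target for QALYs or the ICER. Its sample size does reproduce, and it supplies the effective numbers used below.

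- A 3-point difference with SD 10, two-sided 5% and 90% power needs 234 students per arm.
- With 25 per school and 20% attrition, 20 are analysed. Design effect = 1 + 19 × 0.03 = 1.57.
- 2 × 234 × 1.57 = 735; 735 / 0.8 = 918; 918 / 25 = 36.7 schools, rounded up to 38 for equal arms.
- Adding the two schools that may be lost gives 40 schools and 1000 students, as stated.

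**Effect of adjustment on the standard error (SE).** Assume QALY = T(U0 + U1)/2, equal utility SD s at both times, and baseline/follow-up correlation r.

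- Unadjusted variance: T²s²(2 + 2r)/4 = T²s²(1 + r)/2.
- Variance given U0: T²s²(1 − r²)/4.
- Variance ratio: (1 − r)/2. SE ratio: √((1 − r)/2), which does not depend on T or s.

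If QALYs used follow-up utility alone, the SE ratio would be √(1 − r²).

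| r (assumed) | SE ratio, two-point QALY | SE ratio, follow-up only |
|---|---|---|
| 0.3 | 0.59 | 0.95 |
| 0.5 | 0.50 | 0.87 |
| 0.7 | 0.39 | 0.71 |

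The cuts for r from 0.3 to 0.7 are therefore about 41% to 61% in the first case and 5% to 29% in the second.

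A simulation with 19 schools per arm, 20 students per school and an intracluster correlation (ICC) of 0.03 (1500 runs) gave 0.60, 0.50 and 0.39 for the two-point QALY. At r = 0.5 the ratio ranged from 0.42 to 0.55 as the school-level correlation went from 0.9 to 0.2.

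**Size of chance imbalance (illustration).** Assumptions not in the article: utility SD 0.20, r = 0.5, and the primary outcome's ICC of 0.03 borrowed for utility. T = 8/52 is the upper end of the follow-up window.

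- SE of the baseline utility difference, 380 analysed per arm: 0.20 × √(2 × 1.57/380) = 0.018.
- QALY shift from a one-SE imbalance through U0 alone: 0.018 × (8/52)/2 = 0.0014.
- Including carry-over to follow-up: 0.0014 × (1 + 0.5) = 0.0021.
- For comparison, an assumed true gain of 0.03 in follow-up utility is worth 0.03 × (8/52)/2 = 0.0023 QALY.
- Imbalance needed to cancel that gain: 0.0023/0.0021 = 1.1 SE in the unfavourable direction.

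Using all 1000 students, 25 per school (design effect 1.72), the SE is 0.20 × √(4 × 1.72/1000) = 0.0166, the shift is 0.75 × 0.0166 × 8/52 = 0.0019, and the gain is cancelled at 0.0023/0.0019 = 1.2 SE.

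**Costs.** The article gives nothing on the spread of costs or their correlation over time, so no comparable figure can be calculated.

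**The case against.** The best counter-argument is that the article never calls the differences raw or unadjusted. It names generalized linear models, which are the usual vehicle for covariates, and the ICER sentence is the standard definition of the ratio, equally compatible with model-based differences. The covariate list and the QALY formula may be in a full protocol or analysis plan that is not shown. This stands in part: a reader might infer that the plan commits to an unadjusted ICER, and the text does not go that far. However, it does not tie the models to the ratio either, and resampling observed pairs leans towards an unadjusted analysis. If the models are adjusted and the ratio is not, the two sets of results could disagree.

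Three further limits also stand.

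- A reader might infer that precision is about half what it could be. That holds only for the SE, only with a two-point QALY, and only for r near 0.5.
- A reader might infer that ordinary chance imbalance reverses the sign of the denominator. At one SE it does not in this illustration; about 1.1 to 1.2 SE in the unfavourable direction is needed, and the gain and SD are assumed.
- Over repeated randomisations, chance imbalance does not bias an unadjusted QALY difference. It adds variance, which the bootstrap and acceptability curve are meant to display.

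**Conclusion.** The point holds as a recommended improvement to the economic analysis as it is written. The stated ICER and bootstrap name no baseline adjustment, the baseline measures are collected, and the trial already adjusts the same CHU-9D for baseline in its clinical analysis.

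The reduction in the SE of the QALY difference is large if QALYs are a two-point area under the curve and more modest if they rest on follow-up utility alone. Both ranges depend on an assumed correlation of 0.3 to 0.7. For costs, adjustment is reasonable by analogy, but its benefit cannot be sized from the article.

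The documents do not show that the ICER is wrong, or that it is biased by chance imbalance. Baseline adjustment also gives some protection if consent after randomisation produces arms that differ systematically, but it cannot be relied on to remove such selection. The primary and secondary outcome analyses are unaffected.

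**What to change.** State in the economic analysis, before any data are analysed:

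1. How the two CHU-9D utilities are combined into a QALY.
2. That incremental QALYs come from a model with study group, baseline CHU-9D utility and the stratification factors.
3. That incremental costs come from a model with study group, baseline resource-use cost and the same factors.
4. That the ICER, the bootstrap intervals, the cost-effectiveness plane and the acceptability curve all use these adjusted differences, with both models refitted in each bootstrap sample and schools, not students, resampled.

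If the unseen analysis plan already does this, one sentence in the protocol saying so is enough. The cost is wording and code; every covariate is already in the baseline questionnaire or the randomisation record.

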### Trial design {8}

This study is a stratified cluster randomized controlled trial with two parallel groups. Schools will be randomized to the intervention group and waitlist control group with a 1:1 allocation stratified by location of the schools (rural or urban), state (Victoria, NSW, or WA), and mode of workshop delivery (face-to-face or online),

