### Sample size {14}

For 90% power and a two-sided 5% significance level, a sample of 1000 participants across 40 schools (a minimum of 25 students on average per school) will be required to detect a standardized effect size of 0.3 in mean change in GHSQ score between the study groups. This is equivalent to a 3-point difference in mean GHSQ score between the study groups (standard deviation of 10), which was found in the recent Man Up trial with adult men [30]. Sample size accounts for the correlation of outcomes within schools of 0.03 [31] and assumes 20% attrition at follow-up of students and allows for the potential loss of two schools over the period of the study.

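### The economic analysis, as specified, makes no allowance for school clustering, so its stated uncertainty is likely to be too small

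*Protocol article*

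**What the plan says.** The protocol article treats the school as the unit of design in three places:

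- Trial design {8}: "Schools will be randomized to the intervention group and waitlist control group with a 1:1 allocation".
- Sample size {14}: "Sample size accounts for the correlation of outcomes within schools of 0.03".
- Statistical methods {20a}: the primary model is a linear mixed model "with random effects for school and fixed effects for study group", and the secondary outcomes, including quality of life, are to be analysed similarly.

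The Economic evaluation section is written separately and names its own methods. For the models: "Generalized linear models will be used to assess mean difference in costs and QALYs in the two study groups". For uncertainty: "nonparametric bootstrapping from the distribution of the observed cost/QALY pairs (e.g., 1000 simulated replications) to determine confidence intervals (CIs", with the results shown on a cost-effectiveness plane and an acceptability curve. Neither sentence mentions the school.

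The Economic outcomes text under {18a} says that resource use and unit costs give a total for each student, so the cost/QALY pairs are student-level observations. The economic sensitivity analyses in {20b} vary cost and delivery inputs and compare complete-case with intention-to-treat results. They do not address clustering.

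**The concern.** In a cluster randomised trial, the variance of a difference between arms includes a between-school component. A bootstrap that draws students independently breaks up the schools and loses most of that component. A GLM with ordinary standard errors does the same. The intervals for incremental cost and incremental QALYs then come out too narrow, the cloud of points on the cost-effectiveness plane is too tight, and the acceptability curve is too steep, with probabilities pushed towards 0 or 1.

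Some clustering of costs is plausible from the protocol itself. The intervention description {11a} says that workshops are given to groups, usually by one facilitator per school, and that delivery mode and facilitator travel differ between schools. Every uncertainty statement in the cost-utility analysis depends on how resampling is done.

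**Working it through.** **1. The plan's own sample size.** Inputs from Sample size {14}: "For 90% power and a two-sided 5% significance level, a sample of 1000 participants across 40 schools"; an average of at least 25 recruits in each school; "equivalent to a 3-point difference in mean GHSQ score between the study groups (standard deviation of 10"; ICC 0.03; 20% attrition; two schools lost.

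- Individually randomised: n per arm = 2 × (1.960 + 1.282)² × 10² / 3² ≈ 234.
- Completers per school: 25 × 0.8 = 20.
- Design effect: DE = 1 + (20 − 1) × 0.03 = 1.57.
- Schools per arm: 234 × 1.57 / 20 = 18.4, rounded up to 19. In total 38, plus 2 for loss = 40 schools, and 40 × 25 = 1000 students.

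The stated figure is reproduced exactly. Without the clustering allowance it would be 2 × 234 / 0.8 = 585 students, so clustering is material by the plan's own reckoning.

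**2. Effect on the economic intervals.** With m = 20 completers per school, the student-level standard error is too small by a factor 1/√DE. The coverage of a nominal 95% interval is 2Φ(1.96/√DE) − 1. The protocol gives no ICC for costs or QALYs. The value 0.03 is carried over from the primary outcome, and the other values are an assumed range.

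| ICC | DE = 1 + 19 × ICC | 1/√DE | Interval too narrow by | Coverage |
|---|---|---|---|---|
| 0 | 1.00 | 1.00 | 0% | 95% |
| 0.01 | 1.19 | 0.92 | 8% | 93% |
| 0.03 | 1.57 | 0.80 | 20% | 88% |
| 0.05 | 1.95 | 0.72 | 28% | 84% |
| 0.10 | 2.90 | 0.59 | 41% | 75% |

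With 25 analysed per school and ICC 0.03, DE = 1.72, intervals are 24% too narrow and coverage is 86%. These figures apply to a mean difference in cost or in QALYs. The ICER and the acceptability curve inherit the understatement, but not necessarily the same percentages.

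**3. Simulation check.** Setting: 19 schools per arm, 20 students each, ICC 0.03, normal data, 1000 simulated trials with 300 bootstrap replicates each. The student-level bootstrap covered 85% (mean width 0.279 SD). Resampling whole schools covered 92% (mean width 0.336 SD). The simulation error is about 1 percentage point (√(0.85 × 0.15 / 1000) = 0.011). The direction and rough size agree with the table.

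**4. Which cluster bootstrap.** Drawing schools and then students within school, without correction, counts the within-school variance twice. Take total variance 1 and ICC 0.03:

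- The true variance of a school mean is 0.03 + 0.97/20 = 0.0785.
- The two-stage scheme gives about 0.0785 × 18/19 + 0.0485 × 19/20 = 0.0744 + 0.0461 = 0.1205.
- The standard error ratio is √(0.1205 / 0.0785) = 1.24.

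Simulation gave standard errors about 23% too large and about 98% coverage at ICC 0.03, about 31% too large at 0.01 and about 18% at 0.05. Resampling whole schools gave a ratio of about 0.96, close to the expected √(18/19) = 0.97.

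**The case against.** The strongest reply is that the section is silent on clustering and does not reject it. It is a four-sentence summary in a journal article. The article says that a fuller protocol exists, and it promises a statistical analysis plan. Resampling pairs says first of all that cost and QALY stay together. A GLM is a model family that can carry school-clustered standard errors. Recording cost per participant fixes the level of measurement, not the level of resampling.

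This stands to the extent that a reader might infer that the plan expressly adopts a student-level bootstrap and unclustered GLMs. It does not say so, and a fuller plan could add the school. But the section does fix the model family, what is resampled, an indicative number of replicates and the outputs. The deferral to the analysis plan in {20c} lists additional analyses, non-compliance, missing data and sensitivity analyses, and not the main economic analysis or its clustering. An analyst who followed the text as written would most naturally resample students.

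Two further inferences are not supported:

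- A reader might conclude that the same utility data are analysed once with clustering and once without. The protocol uses the same instrument (CHU-9D) for quality of life and for QALYs, but it does not say that the secondary outcome is scored as a utility.
- A reader might take the largest figures in the table as the expected error. With no ICC given for costs or QALYs, the low end is as admissible as the high end, and at 0.01 the error is small.

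**Conclusion.** The point holds as an omission in the stated economic methods that needs correcting before analysis. On the natural reading, the uncertainty of the cost-utility results is understated, by about 20% of interval width if costs and QALYs cluster as strongly as the plan assumes for the primary outcome. Across the assumed ICC range of 0.01 to 0.10 the shortfall runs from about 8% to 41%, and it vanishes only at an ICC of zero. The figures assume 20 completers in every school and a simple comparison of means.

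The reach is limited. The omission does not bias the point estimates of incremental cost, QALYs or the ICER. The primary and secondary effectiveness analyses already carry a school random effect and are unaffected. No formal economic test or decision threshold is stated that would turn on the interval width.

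**What to change.** Amend the Economic evaluation section, or settle the matter in the analysis plan before the data are analysed:

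- **Bootstrap.** Resample whole schools, separately within each arm, keeping each student's cost/QALY pair intact. A two-stage bootstrap with shrinkage correction is an acceptable alternative. An uncorrected one is not, because it overstates the variance.
- **Models.** Fit the cost and QALY models with a school random effect or school-clustered standard errors.
- **Small number of schools.** With about 19 to 20 schools per arm, apply a small-sample correction, since the simple whole-school bootstrap covered about 92% in the simulation.

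Report the estimated ICCs for costs and QALYs, so that readers can see how much clustering there was. No new data are needed. The cost is a few sentences, a few lines of code and somewhat wider intervals.
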